CSQ-8		X	
Self-reported service usage		X	X
Objective service usage		X	X
Open-ended service acceptability		X	
Open-ended burnout	X	X	X

In the blended care arm, participants will be asked to complete an additional OLBI and DASS-21 if their first consultation is arranged for more than three weeks after their baseline survey is completed. This measure will be provided to participants two weeks before their first consultation date. This will ensure the primary outcome remains valid despite delays to treatment start in the blended care arm (e.g., due to treating clinicians being at capacity or participants' availability), as well as provide treating clinicians with updated data on participants’ current mental health.

To aide participant retention, participants will be reimbursed for their participation by means of a $25 digital gift card sent via the GiftPay system to their nominated email at the completion of each measurement point (i.e. baseline, post-treatment, and 3 months post-treatment). To minimise attrition, participants who do not return survey data will receive up to 3 automated survey reminders via email every 2 days from the initial survey invitation date. Those who do not return survey data after 2 weeks past the final automated reminder will receive a final reminder from a member of the research team sent from the trial email account. To further aide engagement in the in the blended care arm, participants will liaise with a member of the research team or patient care coordinator from the Black Dog Institute Clinical Service regarding consultations and attendance (e.g. organising of consultations in a piecemeal manner when a participant cannot commit to all 5 sessions from initial contact due to scheduling issues, rescheduling of cancelled appointments, etc).

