### Sample size

2.12

We will enrol 207 participants to complete the trial. This sample size is sufficient to examine the primary outcome using repeated measures ANOVA of whether the blended care version of the Navigating Burnout program leads to significantly lower burnout between baseline and 3 months post-intervention compared to self-guided treatment based on a power analysis (α = .05 and power = 0.80) using a conservative medium effect size of f = 0.25 between groups estimating a sample size of 53 per arm (WebPower). As there is limited literature on the effect of blended care treatments for burnout relative to self-guided digital psychotherapeutic programs, a medium effect size of f = 0.25 was chosen as a minimum clinically meaningful effect [28]. Accounting for a conservative estimate of 30% attrition based on previous research health professionals [19], 69 participants are required in each arm leading to a total sample size of 207.

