### Statistical methods

2.13

Study analyses will follow an intention-to-treat analysis plan using multiple imputation to account for missing data. To understand baseline variation and ensure experimental rigor, baseline scores on all psychosocial and occupational outcomes will be checked for between arm consistency using one-way analysis of variances (ANOVAs).

For the primary outcome (changes in OLBI burnout scores), between group variations (i.e., reductions in burnout between arms) will be examined using a 3 (blended, self-guided, active attention control) x 2 (baseline, 3 months post-treatment) mixed model ANCOVA controlling for gender, age, profession, and regionality and explored with pairwise comparisons. Identically formatted mixed model ANCOVAs will be used to analyse the secondary aims and outcomes of between arm and baseline to post-treatment and 3-month post-treatment differences in DASS (anxiety and depression), WSAS (psychosocial functioning), WHO-HPQ (workplace participation), and TIS-6 (attrition intention). The secondary aim and outcomes of comparing service acceptability between arms will be analysed using one-way ANOVAs.

If primary outcome data (i.e. OLBI at 3 months post-treatment) is unavailable for more than 5% of participants from the intention-to-treat population then exploratory and sensitivity analyses will be conducted. The following exploratory analyses of missing primary outcome data will be conducted to inform missingness categorisation and missing data handling: comparing proportion of attrition between arms, reasons for withdrawal, and baseline characteristics between those with and without the primary outcome. Best-worst and worst-best case sensitivity analyses will also be conducted alongside sensitivity analyses using last observation carried forward. Based on the results of these exploratory and sensitivity analyses, either complete case analysis or multiple imputation with 100 imputed data sets of the primary outcome will be conducted.

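### Last observation carried forward is a poor check on the 3-month OLBI result because it moves with retention, and it should not help choose the primary missing-data method

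*Protocol article*

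**What the plan says.** Section 2.13 (Statistical methods) opens without condition: "Study analyses will follow an intention-to-treat analysis plan using multiple imputation to account for missing data". Further analyses are added if the 3-month OLBI "is unavailable for more than 5% of participants from the intention-to-treat population". These begin with descriptive work: attrition by arm, reasons for withdrawal, and baseline characteristics of those with and without the outcome. Next come extreme-case bounds and, with them, "sensitivity analyses using last observation carried forward". The section closes with the decision rule for the 3-month OLBI: "Based on the results of these exploratory and sensitivity analyses, either complete case analysis or multiple imputation with 100 imputed data sets".

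Three other sections bear on this:

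- Section 2.12 (Sample size) plans 69 per arm: "Accounting for a conservative estimate of 30% attrition".
- Section 2.8 (Procedure) describes support given to one arm only, introduced by "To further aide engagement in the in the blended care arm". It concerns arranging and attending consultations. The gift cards and survey reminders in the same section are not arm-specific.
- Section 4 (Results) expects burnout to improve in both intervention arms, more so in the blended arm, and expects the control to be essentially inert apart from some incidental improvement.

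**The concern.** OLBI is measured at baseline, post-treatment and 3 months. Carrying the last value forward assigns exactly zero change to a participant with only a baseline score, assigns the post-treatment score to one lost later, and treats both as if they had been observed. If scores improve over time, an arm that keeps more participants is credited with more of that improvement. The estimate then mixes the treatment effect with the retention difference. The direction of the error depends on which arm loses more people, so neither agreement nor disagreement with the main analysis says anything reliable about robustness.

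Two things are at stake. The first is a sensitivity result that will be read as a plausible estimate when it is not one. The second is that this result, which is an unblinded comparison of arms on the primary outcome, is among the inputs to the choice of primary method.

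**Working it through.** **Will the analysis be run?** The plan expects 30% attrition: 0.30 × 207 ≈ 62 participants. The trigger is more than 5%: 0.05 × 207 = 10.35, so 11 or more. On the plan's own figure it will be run.

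**Inputs.** From the documents: 69 per arm, three measurement times, and improvement expected in both intervention arms. The documents give neither arm-specific dropout nor a size of change, so both are assumed over a range. The plan states no figure for this analysis that could be reproduced.

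**Formula.** Let d be dropout, c the true improvement in SD units, s the share of dropouts with a post-treatment score (with the post-treatment improvement equal to that at 3 months), and B and S blended and self-guided. The expected difference after carrying forward is

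cB × [1 − dB(1 − s)] − cS × [1 − dS(1 − s)].

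**A true difference of 0.50 SD (cB = 0.75, cS = 0.25), s = 0.**

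- Dropout 30%/30%: 0.70 × 0.75 − 0.70 × 0.25 = 0.35
- Dropout 20%/40%: 0.80 × 0.75 − 0.60 × 0.25 = 0.45
- Dropout 40%/20%: 0.60 × 0.75 − 0.80 × 0.25 = 0.25

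The same true effect gives 0.25 to 0.45 depending only on retention. At 30%/30% with s = 0.5, the shrinkage is milder: 0.50 × 0.85 = 0.425.

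**No true difference (cB = cS = c).** The formula reduces to c(1 − s)(dS − dB). It is zero if dropout is equal or if c = 0. The rejection rates below come from simulation (69 per arm, dropout completely at random, correlations 0.6 to 0.7 between time points, t test on change, 5,000 runs).

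| c (SD) | Dropout B/S | Spurious difference, s = 0 | Rejection, s = 0 | Spurious difference, s = 0.5 | Rejection, s = 0.5 |
|---|---|---|---|---|---|
| 0 | 20%/40% | 0 | about 5% | 0 | about 5% |
| 0.5 | 30%/30% | 0 | about 5% | 0 | about 5% |
| 0.5 | 20%/40% | 0.10 | 12.7% | 0.05 | 6.3% |
| 0.8 | 20%/40% | 0.16 | 20.3% | 0.08 | 7.7% |

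**Check by hand at correlation 0.5, s = 0.** The SD of change is then 1, and the variance of the carried-forward change in an arm is (1 − d) + d(1 − d)c².

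- c = 0.5: variances 0.84 and 0.66; SE = √(1.50/69) = 0.147; 0.10/0.147 = 0.68; two-sided rejection about 10%.
- c = 0.8: variances 0.902 and 0.754; SE = √(1.656/69) = 0.155; 0.16/0.155 = 1.03; rejection about 18%.

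The range for s = 0 is therefore about 10% to 20% across these correlations. Complete case analysis of the same simulated data stayed at about 5%, as it must when dropout is completely at random.

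**The case against.** The strongest reply is that carrying forward can never supply the primary estimate: section 2.13 restricts that to complete case analysis or multiple imputation. This stands. A reader might infer from the table that the trial's own false-positive rate is 10% to 20%. The documents do not support that, because the rates describe one sensitivity analysis, computed with a t test on change and not the planned mixed ANCOVA. Nor has it been shown that its result would lead to the worse primary method.

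A reader might also infer that the blended-only support in section 2.8 makes unequal outcome retention likely. The text does not go so far. That support concerns consultations. Survey reminders and gift cards are not arm-specific, the self-guided arm has fortnightly programme reminders (section 2.3), and the control emails follow the same rhythm (section 2.4). Unequal retention is a possibility, which section 2.13 itself recognises by planning to compare attrition between arms. The 20%/40% split is an assumption.

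Nor can one infer that scores will fall in every arm. Section 4 expects an inert control, and entry is by self-reported burnout with no OLBI threshold (section 2.2). The mechanism is therefore argued here for blended versus self-guided only. If the control hardly changes, carrying forward mainly shrinks comparisons against it.

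Finally, the larger rates need all dropout to precede the post-treatment survey. With half of it later, they fall close to nominal.

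These points limit the size of the problem. They do not make the method informative: its error has no fixed direction, and its result is still a stated input to the primary choice.

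**Conclusion.** The concern holds in this limited form. Carrying forward is an uninformative check on blended versus self-guided, because under the protocol's own expectation of improvement in both arms its estimate moves with any retention difference, and with equal dropout it understates a true effect (0.35 instead of 0.50 SD at 30% early dropout). With no true difference and 20%/40% dropout, the spurious effect is 0.10 to 0.16 SD, with rejection of about 10% to 20% if all dropout is early. If half of dropouts have a post-treatment score, it is 0.05 to 0.08 SD, with rejection of about 6% to 8%. It vanishes with equal dropout or no change. The dropout split and the amounts of change are assumptions.

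The more consequential fault is in the wording around it: results by arm are allowed to steer the choice of primary method, in conflict with the unconditional multiple imputation at the start of the same section. The change is worth making, but nothing here invalidates the primary test.

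**What to change.** Three changes to section 2.13:

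1. Name multiple imputation as the primary method, as the opening sentence already does, with arm, baseline OLBI and post-treatment OLBI in the imputation model.
2. Replace carrying forward with delta-adjusted versions of the 100 planned imputations: worsen the imputed 3-month OLBI by fixed amounts, set separately by arm (for example 0.1 to 0.5 SD), and report the shift at which the conclusion changes. This tests departures from missing at random directly.
3. Delete the rule that picks the primary method from the exploratory and sensitivity results. Keep the attrition comparisons as description, and report all sensitivity results beside the primary one.

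The cost is a few sentences of text, a grid of shifts fixed in advance, and a few reruns of an imputation already planned. No extra data or participants are needed.

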### Primary outcome

2.9

The primary outcome will be self-reported burnout, as measured by the OLBI, with the primary endpoint being 3 months post-treatment.

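### The primary missing-data method is first fixed as multiple imputation, then left to be chosen from results that include treatment-effect estimates

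*Protocol article*

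**What the plan says.** The primary outcome is the OLBI, "with the primary endpoint being 3 months post-treatment" (section 2.9). The primary model is a "3 (blended, self-guided, active attention control) x 2 (baseline, 3 months post-treatment) mixed model ANCOVA", followed by pairwise comparisons (section 2.13).

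Section 2.13 deals with missing data twice. Its first sentence is a general commitment: "Study analyses will follow an intention-to-treat analysis plan using multiple imputation to account for missing data". Its last paragraph sets a separate route for the primary outcome. If the 3-month OLBI "is unavailable for more than 5% of participants from the intention-to-treat population then exploratory and sensitivity analyses will be conducted". The exploratory part is "comparing proportion of attrition between arms, reasons for withdrawal, and baseline characteristics between those with and without the primary outcome", and its declared purpose is to judge the type of missingness and how to handle it. The sensitivity part reads: "Best-worst and worst-best case sensitivity analyses will also be conducted alongside sensitivity analyses using last observation carried forward". The paragraph then closes the loop: "Based on the results of these exploratory and sensitivity analyses, either complete case analysis or multiple imputation with 100 imputed data sets". Whichever is chosen is then run on the 3-month OLBI.

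**The concern.** Both statements cannot govern the primary analysis. The first fixes imputation; the second allows it to be dropped in favour of complete case analysis.

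The second statement also reverses the usual order. A sensitivity analysis tests a primary analysis that is already fixed. Here its results help to select the primary analysis. Best-worst, worst-best and last observation carried forward (LOCF) each fill in the missing 3-month scores and return a between-arm contrast on the primary endpoint. Whoever makes the choice will therefore have seen estimates of the treatment effect.

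Two things are at stake: the nominal error rate of the primary test, and the possibility that the method chosen is the one more exposed to bias from selective dropout.

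**Working it through.** **1. The two statements side by side.** With 5% or less missing, only the opening sentence applies and imputation is fixed. With more than 5% missing, either method may be used. The commitment to imputation is firm where it matters least and open where it matters most.

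**2. Will the 5% trigger be reached?** Inputs from section 2.12: f = 0.25, "α = .05 and power = 0.80", 53 per arm, 30% attrition, 69 per arm, 207 in total. The plan's figure reproduces. For a three-group between-arm F test with noncentrality N × f², 80% power needs N = 158, and 158/3 = 52.7, so 53 per arm. Then 53 × 1.30 = 68.9, so 69, and 3 × 69 = 207. (How the attrition allowance is applied is a separate matter and does not affect this check.)

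- Expected missing: 0.30 × 207 = 62.1.
- Trigger: 0.05 × 207 = 10.35, so 11 or more missing.
- Binomial probability of 11 or more out of 207: above 0.9999 at 30% attrition, 0.995 at 10%, 0.46 at 5%.

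**3. What could the choice cost?** The simulation assumed no treatment effect and used one pairwise contrast as a stand-in for the three-arm model: 69 per arm, 6000 runs per scenario, 3-month OLBI regressed on arm and baseline OLBI. Complete case was compared with 100 imputations pooled by Rubin's rules (T = W + (1 + 1/100) × B). Assumed correlations were 0.5 between baseline and each later visit, and 0.7 or 0.8 between post-treatment and 3 months. Post-treatment OLBI was taken as observed for everyone. In the last scenario, logit P(missing) = ln(0.3/0.7) ± 0.5 × standardised post-treatment OLBI, with opposite signs in the two arms.

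| Scenario | Complete case | Imputation | Significant under either | Methods disagree |
|---|---|---|---|---|
| Completely at random, 30%, post-treatment OLBI in imputation model, correlation 0.7 | 0.051 | 0.049 | 0.065 | 0.030 |
| Same, correlation 0.8 | 0.048 | 0.045 | 0.065 | 0.038 |
| Completely at random, 30%, correlation 0.7, post-treatment OLBI not in imputation model | 0.051 | 0.050 | 0.054 | 0.006 |
| Completely at random, 10%, correlation 0.7, post-treatment OLBI in imputation model | 0.052 | 0.050 | 0.059 | 0.015 |
| Dropout depends on post-treatment OLBI, opposite by arm, correlation 0.7, post-treatment OLBI in imputation model | 0.110 | 0.043 | 0.128 | 0.102 |

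The Monte Carlo standard error near 0.05 is √(0.05 × 0.95/6000) = 0.003.

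The fourth column is an upper bound. It supposes that both results are seen and the favourable one is reported.

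**4. A rule closer to the text.** As written, LOCF and best/worst-case results are seen first, and then one method is run. In a similar null simulation (69 per arm, 30% missing completely at random, 4000 runs, 20 imputations), choosing imputation when LOCF was significant and complete case otherwise gave 5.4-5.8%. The reverse rule gave 3.9-4.9%.

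**5. Reading the results.** Under random dropout the selection effect is small. In the last scenario most of the excess comes from complete case itself (0.110 of the 0.128), so the main danger is which method is selected rather than the act of selecting. The third row shows that imputation without the post-treatment score behaves almost exactly like complete case.

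**The case against.** The strongest defence is that the choice rests partly on legitimate grounds. Attrition by arm, withdrawal reasons and baseline differences between those with and without the outcome are not treatment effects, and using them to judge missingness is defensible. This stands. The fault is confined to letting the sensitivity results share in the decision.

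It can also be said that the first sentence is general and the last paragraph a specific exception, and that the analysis plan, which is not shown, may hold a decision rule. The missing criterion is therefore not the point. What the protocol does state is that the results decide, and that leaves the primary outcome with a weaker commitment than the other outcomes.

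Three stronger readings are tempting, and the documents do not support them.

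- A reader might infer that the choice is made unblinded. Section 2.7 on blinding concerns participants only and says nothing about the analyst. The point does not need it: these analyses require data split by arm, and masked codes would still show whether the arms differ.
- A reader might put the error rate at 6.5-7.8%, the chance that either of two tests correlated 0.95 to 0.80 is significant. That models a free pick between two visible results, which is not the procedure described. At the simulated correlation of 0.94 even that bound is about 6.6%.
- A reader might say that best-worst and worst-best must always disagree and so carry no information. With assumed extremes at ±2 SD, each shifts the contrast by 0.30 × 4 = 1.2 SD at 30% missing, but only 0.10 × 4 = 0.4 SD at 10%. The claim depends on both assumptions.

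**Conclusion.** The plan is wrong as written. Section 2.13 contradicts its own commitment to imputation, and for the primary endpoint it makes the method depend in part on estimated between-arm effects. At the attrition that the protocol itself plans for, the rule is near certain to come into play.

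The size depends on why data go missing. If they are missing completely at random, the harm is modest, with an upper bound of about 5.4-6.5% against a nominal 5%. If dropout depends on post-treatment burnout differently by arm, selecting complete case is the serious outcome: about 11% type I error, against about 4% for imputation that uses the post-treatment score. That contrast rests on an assumed dropout model, assumed correlations and a complete post-treatment visit. Imputation would protect less if many participants miss both follow-up surveys. The figures show what could happen; they do not forecast what will happen in this trial.

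**What to change.** Delete the sentence that selects the method from the results. State that the primary analysis uses the multiple imputation already promised, with 100 data sets, whatever the percentage missing, and that the imputation model includes post-treatment OLBI, which Table 1 shows is collected in all arms. Keep complete case, LOCF and best-worst/worst-best as named sensitivity analyses. Keep the attrition and baseline comparisons as descriptive. Say that none of these can change the primary method. Replacing LOCF or the best/worst-case analyses with another approach is a matter of preference and is not needed to correct the error.

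The cost is a few sentences in the protocol and analysis plan and slightly more programming, with no added data collection. The change should be made before any 3-month outcome is examined by arm, because it cannot be made credibly afterwards.
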